### 2.7. Neuroimaging

Baseline and post-intervention images will be acquired using a 3.0 T device (Achieva, Phillips, Amsterdam, The Netherlands) located at the Radiology Institute of the Hospital das Clínicas of the Faculty of Medicine of the University of São Paulo (USP). The device is equipped with a Quasar Dual gradient system (maximum intensity of 80 mT/m and variation rate of up to 200 mT/m/ms) and a dedicated 8-channel skull coil with availability of the SENSE technique. Paramagnetic contrast medium will not be administered, and head position will be secured with foam padding to minimize movement. During the approximately 60 min procedure, cardiac and respiratory monitoring will be performed to eliminate possible physiological noises from these sources in the image pre-processing stages [54]. Patients will be instructed to keep their eyes closed, not move, and think as little as possible during the exam.

The anatomical dataset will include T1-weighted structural MRI sequences acquired for voxel-based morphometry (VBM) analysis. Group comparison statistics for each voxel of brain volume can be performed using VBM, allowing the quantification of the local volume of white or gray matter and automated extraction of regions of interest (ROIs) [55]. The assessment of cortical thickness in ROIs will also be performed. Additionally, diffusion-weighted images (DWIs) will be obtained to measure the anisotropy/isotropy index and the diffusivity of water molecules and to evaluate structural connectivity. Resting-state functional MRI (rsfMRI) based on the blood-oxygen-level-dependent (BOLD) effect will also be acquired to assess functional connectivity.

The volumetric weighted 3D T1 images will be recorded using the following parameters: repetition time (TR) = 7.0 ms, echo time (TE) = 3.2 ms, angle of inversion (FA) = 8°, direction 1.5, field of view (FOV) = 240 × 240 mm, matrix = 240 × 240 pixels, 180 slices of 1 mm each, no gap, producing a voxel size of 1 mm × 1 mm × 1 mm. A weighted FLAIR sequence high-resolution T2 will also be collected to increase accuracy for automatic segmentation of structures. These images can be used in the following configurations: TE = 120 ms, TR = 2800 ms, 60 axial slices (thickness = 3 mm), AF = 8°, FOV = 230 mm × 230 mm.

The DWI will be collected using an EPI sequence single-shot (echo planar imaging) with 64 directions of non-collinear gradients (sampled across the sphere) through a b-shell (b = 1000 s/mm^2^) plus 08 volumes B0 (no broadcast) interleaved. The following parameters will be defined: TE = 100 ms, TR = 8801 ms, angle of inclination = 90°, FOV = 256 mm × 256 mm, acquisition matrix = 256 × 256, 64 slices, slice thickness = 2.0 mm (no gap between slices), yielding a size of 2 mm × 2 mm × 2 mm voxel. 

We will acquire rsfMRI using the EPI T2*-weighted sequence, with the following parameters: SENSE 2, TR = 2200 ms, TE = 28 ms, 3 mm slice thickness, 3 mm isometric voxel size, 0.3 mm slice interval, FOV of 240 × 240 × 125, and a frame size of 80 × 80 matrix. This sequence will result in 38 slices/volume and a total of 300 volumes. To minimize motion effects, we will use stabilizer dynamics. 

We will store the processed images in DICOM format to facilitate data sharing [56], anonymized by removing facial features, and transfer them to our dedicated workstation. We will perform a quality check, pre-process the images, and analyze them with different software, including FSL 4.1 (FMRIB, Oxford, UK), Freesurfer 7.4.1 (Computational Neuroimaging Laboratory, Harvard Medical School, Cambridge, MA, USA), SPM 12 (Wellcome Department of Imaging Neuroscience, London, UK), and internal scripts based on image type (e.g., structural, functional).

Cortical brain volume, area, and cortical thickness will be quantified for the dorsal prefrontal cortex (DLPFC) and subgenual anterior cingulate cortex (sgACC) using the Glasser parcellation [57]. Subcortical brain volume will also be quantified for the hippocampus and amygdalae. These regions were selected based on previous studies [58,59,60]. Both subcortical and cortical volumes will be divided by the total intracranial volume (TIV) to control for differences in brain size among participants. Structural and functional connectivity will be carried out using these ROIs as seeds. 

Statistical analyses will be performed using R Version 4.1.2. We will use linear mixed models with a three-way interaction between the fixed predictors MRI measure, time (pre-treatment and post-treatment), and treatment (ECT group vs. MST group). Participants will be included as random effects. All results will be considered significant at a p threshold of 0.05. Outcomes will be the HAMD-17 scores. To each three-way significant interaction, we will perform two-way interaction between the fixed predictors MRI measure and time separately to each group. The same analysis will be performed within each treatment group. We will also explore associations between baseline MRI-based biomarkers and ECT and/or MST effectiveness, evaluated with the changes in depression scores measured by HAMD-17 using linear mixed models. All the reported values will be based on the three-way or two-way interaction of the fixed variables.

### 2.8. Seric Biomarkers

Venous blood collections will be performed in the morning, fulfilling a minimum fasting period of 8 h comprising the following events:C1 (Collection 1): Performed on the day corresponding to the first session, prior to the procedure, taking advantage of the need for venipuncture. This will be considered the baseline sample;C2 (Collection 2): performed prior to 6th session;C3 (Collection 3): performed prior to 12th session;C4 (Collection 4): performed prior to 18th session (if any);C5 (Collection 5): performed 12 weeks after the start of the treatment;C6 (Collection 6): performed 24 weeks after starting treatment, coinciding with the 3-month medical evaluation.

Two 4 mL tubes of venous blood samples with anticoagulant (EDTA) will be collected before each event to prevent biochemical alterations related to the convulsive crisis. The collections will be performed at the ECT Service and immediately transported to the Neuroscience Laboratory LIM-27 for proper storage until the biochemical analysis is conducted. Post-treatment collections (C5, C6, and C7) will be scheduled with the staff and patient at the Neuroscience Laboratory LIM-27 after an 8 h fast. Brain-derived neurotrophic factor (BDNF) will be evaluated in the plasma using an immunofluorescence ELISA technique, which is highly specific for this type of evaluation. This technique has been shown to be more appropriate for state-dependent assessment of BDNF levels than other methods [61].

Our primary objective is to explore potential associations between changes in plasma BDNF levels and variations in depressive symptom scores and treatment response, as well as other clinical and neuroimaging outcomes (such as the variation in volume of each ROI). Additionally, we intend to compare the differences in plasma BDNF variation over time in patients undergoing ECT or MST. Moreover, we will evaluate the discrepancies in BDNF levels between patients who respond positively to treatment and those who do not, in each treatment arm.

Based on previous studies [62,63,64,65], our hypothesis is that there will be a progressive increase in plasma BDNF levels, especially in the subgroup of patients with lower BDNF levels at baseline. We also hypothesize that there will be a positive correlation between improvement in depressive symptoms and an increase in BDNF, but its significance will be observed specifically in relation to plasma BDNF collected at time points C5 and C6. Additionally, we believe that higher baseline plasma BDNF levels may be associated with higher rates of treatment response and remission and, possibly, better cognitive outcomes. Furthermore, there will be a similar increase in plasma BDNF levels in patients who undergo ECT when compared to those who receive MST.

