We will define adverse events as events with intensity greater than “mild” and at least “remotely” associated with the intervention, as carried out in our previous studies [31]. The presence of adverse events and (hypo)manic upset will be compared between groups E and C using the chi-square test. This test will also be used to assess whether allocation group guessing occurred beyond chance.

Regarding the BDNF data, each collection during the follow-up will be individually analyzed in relation to the baseline values using Student’s *t*-test. The same analysis will be conducted to assess the differences between the treatment groups (ECT x MST) at each endpoint. Additionally, analysis of variance (ANOVA) will be used to evaluate potential differences in the means of plasma BDNF at different collection time points. A significance level of 5% will be adopted for all tests.

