### 2.10. Sample Size Calculation

The software programs G * Power 3 [67] from Universität Düsseldorf, Germany, and Stata (Statacorp, College Station, TX, USA) were used to conduct calculations. The sample size was determined using parameters of α = 0.025 (one-tailed), β = 0.2, and a standard deviation of 9.5. The margin of non-inferiority (NI) was determined based on a combination of statistical reasoning and clinical judgment [68]. The lower bound of the confidence interval from a meta-analysis comparing ECT vs. sham was used to establish the NI [69]. Using a meta-analysis by the UK ECT Review Group [16], the difference in HAMD17 scores between ECT and placebo was 9.7 points (95% CI 5.7 to 13.5), with an NI value of 5.7. Despite the large margin, this NI value was deemed acceptable due to the cognitive effects of bitemporal ECT (the control comparison). Thus, MST would be a reasonable non-inferior intervention, as cognitive superiority would also need to be demonstrated. The sample size required was 88 patients, with an additional enrollment of 10% (total of 100 patients, 50 per arm) to account for attrition. For the superiority analysis, we used data from an unpublished clinical trial of 75 patients that compared the efficacy and cognitive outcomes of MST vs. ECT (personal communication from [name]). The effect size of AMT [32] after 12 treatment sessions was approximately 1.31, requiring a sample size of 26 patients to demonstrate a difference. Thus, the larger sample size from the clinical outcome study was used for the NI calculation.

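### The plan predicts a similar BDNF rise under ECT and MST but compares the arms only with tests for a difference, which cannot support similarity (minor; exploratory biomarker)

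*Protocol article*

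**What the plan says.** Section 2.8 (Seric Biomarkers) lists a baseline sample, C1, and five later collections, C2 to C6. C4 is taken only from patients who go on to an 18th session. The main BDNF aim is exploratory: associations between BDNF change and symptoms, response and imaging. The comparison of arms comes second: "Additionally, we intend to compare the differences in plasma BDNF variation over time in patients undergoing ECT or MST". The hypotheses at the end of the section include "Furthermore, there will be a similar increase in plasma BDNF levels in patients who undergo ECT when compared to those who receive MST".

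Section 2.9 (Statistical Analysis) sets the BDNF analysis. Each follow-up collection is compared with baseline by Student's t-test. Then: "The same analysis will be conducted to assess the differences between the treatment groups (ECT x MST) at each endpoint". An ANOVA "will be used to evaluate potential differences in the means of plasma BDNF at different collection time points". Finally: "A significance level of 5% will be adopted for all tests".

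Sections 2.9 and 2.10 give non-inferiority margins for HAMD17, response and remission. No margin, interval criterion or equivalence test is given for BDNF.

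**The concern.** The prediction is one of similarity and the test is one of difference. If the arms do not differ significantly at a collection, the planned analysis cannot tell two explanations apart: the rises really are alike, or the sample was too small to show that they are not. The article gives no rule for separating them, so a non-significant p-value is the only result that could be offered in support of the prediction.

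At stake is a secondary statement about mechanism, that both treatments raise BDNF to a like degree. It could be reported although the data are compatible with a moderate difference between arms.

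**Working it through.** **Inputs from the article.** Section 2.10: "The sample size was determined using parameters of α = 0.025 (one-tailed), β = 0.2, and a standard deviation of 9.5"; "the difference in HAMD17 scores between ECT and placebo was 9.7 points (95% CI 5.7 to 13.5), with an NI value of 5.7"; "The sample size required was 88 patients, with an additional enrollment of 10% (total of 100 patients, 50 per arm) to account for attrition". Section 2.9: 5% per BDNF test, taken here as two-sided because sidedness is not stated for BDNF.

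**Inputs assumed.** The article gives no BDNF SD or effect size, so differences are expressed in SD units of the quantity compared. A difference of 0.5 SD serves as the benchmark for moderate.

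**Step 1: reproduce the plan's sample size.** With a true difference of 0 and the normal approximation, n per arm = 2 × (1.960 + 0.842)² × (9.5 / 5.7)² = 2 × 7.85 × 2.78 = 43.6, rounded up to 44. The total is 88, as stated. Allowing for 10% loss, 88 / 0.9 = 97.8, or 98, against the stated 100. The sample was therefore set by a HAMD17 margin of 5.7 / 9.5 = 0.6 SD, and BDNF played no part in it.

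**Step 2: precision of the between-arm BDNF difference.** The 95% half-width in SD units is t(0.975; 2n − 2) × √(2/n).
- 44 per arm: 1.988 × 0.2132 = 0.42 SD
- 50 per arm: 1.984 × 0.2000 = 0.40 SD

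For example, an observed difference of 0.30 SD at 44 per arm is not significant, and its interval runs from 0.30 − 0.42 = −0.12 to 0.30 + 0.42 = 0.72 SD. That result does not show similarity.

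**Step 3: chance of missing a true 0.5 SD difference.** Two-sided 5% t-test, noncentrality 0.5 × √(n/2).

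| Per arm | Noncentrality | Power | Missed |
|---|---|---|---|
| 50 (enrolled) | 2.50 | 69.7% | 30% |
| 44 (evaluable) | 2.35 | 64.0% | 36% |
| 40 (assumed) | 2.24 | 59.8% | 40% |
| 30 (assumed) | 1.94 | 47.8% | 52% |

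The last two rows show the direction at C4, where patients who remit by session 12 contribute no sample. The article gives no per-arm number for C4. A difference test would need 64 per arm for 80% power at 0.5 SD.

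**Step 4: what a margin-based check could show.** Take a margin of ±0.5 SD, again only for illustration, with identical arms and a 90% interval required to lie inside the margin. By the normal approximation, power = 2Φ(0.5 / √(2/n) − 1.645) − 1.
- 44 per arm: 2Φ(2.345 − 1.645) − 1 = 52%
- 50 per arm: 2Φ(2.500 − 1.645) − 1 = 61%
- 80% power needs 69 per arm

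Even with a suitable criterion, this sample would often not settle the question.

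**Step 5: do the other planned analyses help?** The ANOVA across collection times tests for differences in means. Section 2.9 also applies hierarchical models to continuous secondary outcomes. It is unclear whether BDNF is one of these, and as described those models also test for a difference. Neither supplies a criterion for similarity.

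**The case against.** The strongest reply is that the prediction is an informal expectation. It stands among statements of belief, the stated aim is to compare arms, and a difference test suits that aim. Where the trial wants a margin-based claim, it sets a margin. This stands in part: BDNF is exploratory, and no formal equivalence claim is announced. It does not remove the mismatch, because the prediction is stated as a hypothesis and no planned analysis can support it.

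A second reply is that margins and model details for a biomarker belong in the full protocol or analysis plan. That is fair as regards the missing margin, which is not a fault in itself. But the article does fix the test, the occasions and the significance level, and that fixed choice does not fit the hypothesis.

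Three stronger readings are tempting, and the article does not support them:
- A reader might infer that p > 0.05 will be declared to show similarity. No such rule is stated. Equally, no rule says that one significant result among C2 to C6 would refute the hypothesis.
- A reader might infer that a shared neurotrophic response is a headline conclusion of the trial. The Discussion does call overlap between the two treatments the main question, but there it means neuroanatomical overlap.
- A reader might infer that one collection, or a margin of 0.5 SD, is the natural choice. Neither has a basis in the article. Section 2.8 itself singles out C5 and C6 for the correlation with symptoms, so an analysis confined to an earlier collection would leave out time points that the trial stresses.

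**Conclusion.** The point holds in a limited form and is minor. The hypothesis of a similar BDNF rise is paired only with tests for a difference. With 44 to 50 per arm, non-significance leaves room for a moderate difference: the half-width is about 0.42 to 0.40 SD, and a true 0.5 SD difference is missed in about 36% to 30% of trials.

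The half-widths need only the sample size and the 5% level. The miss rates rest also on the assumed 0.5 SD benchmark. Fewer samples at a collection would make both worse. Nothing here touches the co-primary decision on HAMD17 and AMT.

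**What to change.** In section 2.9:

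1. Replace the between-arm t-tests at each collection with the between-arm difference in BDNF change from baseline, adjusted for baseline BDNF and reported with confidence intervals. One longitudinal model over C2 to C6 would do this, and it also matches the stated aim of comparing variation over time.
2. State that a non-significant difference will not be taken as evidence of similarity.
3. State that the rises will be called similar only if the interval lies within a margin that the sponsor prespecifies and justifies, at a collection or over a period that the sponsor names. Otherwise the estimate and interval are reported as inconclusive. If no margin can be justified, report the estimate and interval and make no similarity claim.

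The margin and the decisive collection are for the sponsor to choose.

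The cost is a few sentences of analysis wording, with no new samples or visits. The drawback is that the similarity hypothesis will often end as inconclusive, as the illustrative margin check above shows.

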### 2.9. Statistical Analysis

Statistical analyses will be performed in R. The results will be considered statistically significant only if both conditions are met, that is, non-inferiority for the depression outcome, under unilateral *p* < 0.025, and superiority for the cognitive outcome, under *p* bilateral < 0.05. The following groups will be considered: experimental (E), corresponding to MST, and control/comparison (C), corresponding to ECT.

For the co-primary outcome depression (HAMD17), non-inferiority will be assessed by calculating the difference between the means of groups E and C and its 95% confidence interval at the end of the 12th session, which will then be compared to the NI margin (Ha: C-E < NI). Analyses will be performed on modified intent-to-treat (ITT) samples (at least 8 sessions of ECT/MST) and per-protocol (PP).

For the co-primary cognitive outcome (AMT [32]), we will perform linear hierarchical model analyses using a first-order regressive covariance structure, which includes all observed variables without the need to enter data for missing values. The dependent variable is the AMT score [32], the independent variables are time (all observations through week 6) and group. We will test the statistical significance of this interaction according to our superiority hypotheses controlled for age, years of schooling, and treatment-resistant depression (Ha: C-E < 0). Analyses will be performed on the ITT and PP sample.

The same linear hierarchical models will be used for all continuous secondary outcomes. We will assess response and sustained remission, that is, a clinical improvement of symptoms ≥50% (response) and a HAMD17 score ≤7 (remission) at a given point in the study, which will be maintained until the outcome. The trajectories of response and sustained remission between groups will be compared using Kaplan–Meier survival analysis. Response and remission will be compared considering non-inferiority margins of 20% and 15%, respectively. The choice of a 15% non-inferiority margin was based on the consideration that achieving a remission rate of 35% holds clinical relevance in this population with difficult-to-treat depression. Furthermore, this remission rate surpasses those achieved by more conventional and less invasive treatment options for TDR, such as repetitive TMS (rTMS) with an approximate remission rate of 20% [66] and antidepressants with a remission rate of 14% [1].

We will define adverse events as events with intensity greater than “mild” and at least “remotely” associated with the intervention, as carried out in our previous studies [31]. The presence of adverse events and (hypo)manic upset will be compared between groups E and C using the chi-square test. This test will also be used to assess whether allocation group guessing occurred beyond chance.

Regarding the BDNF data, each collection during the follow-up will be individually analyzed in relation to the baseline values using Student’s *t*-test. The same analysis will be conducted to assess the differences between the treatment groups (ECT x MST) at each endpoint. Additionally, analysis of variance (ANOVA) will be used to evaluate potential differences in the means of plasma BDNF at different collection time points. A significance level of 5% will be adopted for all tests.

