### 2.3. Eligibility Criteria

Trained psychiatrists/psychologists will review the diagnosis of depression using the Brazilian version of the Mini International Neuropsychiatric Interview 5.0.0 (MINI) [19], which was developed based on the *Diagnostic and Statistical Manual of Mental Disorders*, 4th edition (DSM-IV) and International Classification of Diseases and Related Health Problems, 10th revision (ICD-10). 

Inclusion criteria are: (a) age between 18 and 60 years; (b) diagnosis of major depressive disorder or depressive episode in bipolar disorder according to DSM-IV; (c) baseline HAMD17 score ≥17; (d) current TDR episode; (e) appropriate clinical condition for receiving ECT as assessed by a psychiatrist and an anesthesiologist; and (f) meeting transcranial magnetic stimulation (TMS) safety criteria [20]. In the definition of TRD for major depressive disorder, the utilization of a minimum of two prior treatment failures will be considered. Conversely, for TRD in bipolar depression, only one prior treatment failure will be required. In both cases, there must be confirmation of prior adequate dose and duration, based on clinical criteria evaluated using the Antidepressant Treatment History Form (ATHF) [21,22].

Exclusion criteria are: (a) pregnancy; (b) psychiatric comorbidity (except mild anxiety disorders); (c) depressive symptoms better explained by other clinical conditions or psychiatric disorders; (d) decompensated clinical and neurological conditions or serious sequelae of previous medical conditions; (e) use of psychoactive substances in the last 6 months (except nicotine); (f) use of monoamine oxidase inhibitors in the last 6 months; (g) application of ECT or another neuromodulation technique in the last 12 months; (h) contraindications for ECT or MRI; (i) relevant deviations in clinical laboratory parameters; or (j) inability to consent.

Discontinuation criteria are: (a) worsening depression; (b) development of suicidal ideation or suicide attempt; (c) withdraw consent; (d) development of (hypo)manic symptoms; (e) inability to induce seizures lasting at least 15 s after adjusting parameters and medications during the titration phase; (f) missing two consecutive treatment sessions; or (g) changes in drug treatment without the previous authorization.

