## Figures and Tables

**Table 1 biomedicines-11-02150-t001:** Clinical measures.

Measure	Study Period					
	Prior to Acute Phase		Active Phase *	Follow-Up		
	Screening	Baseline		Post-Acute **	3 Months	6 Months
Inform Consent	x					
Demographics Form	x					
ABEP		x				
Medical History Form	x					
ATHF	x					
MINI	x					
QCT		x				
BPI		x				
HAMD17	x	x	x	x	x	x
MADRS		x	x	x	x	x
CGI		x	x	x	x	x
BDI-II		x	x	x	x	
DTS		x	x	x	x	x
BSI		x	x	x	x	x
WHOQOL		x		x	x	x

ABEP, Brazil Criterion of the Brazilian Association of Research Companies 2016 [33]; ATHF, Antidepressant Treatment History Form [22]; MINI, Mini International Neuropsychiatric Interview [19]; QCT, Questionnaire on Childhood Trauma [34]; BPI, Borderline Personality Inventory [35]; HAMD17, Hamilton Depression Rating Scale, 17 items [17]; MADRS, Montgomery–Asberg Scale [36]; CGI, Clinical Global Impression Severity (CGI-S) and Clinical Global Impression Improvement (CGI-I) scales (we will apply both the CGI-S and CGI-I) [37]; BDI-II, Beck Depression Inventory [38]; DTS, Depressive Thoughts Scale [39]; BSI, Beck Suicidal Ideation Scale [40]; WHOQOL, WHO quality of life questionnaire [41]; * after the 6th session; ** one week after the last session (12th or 18th, if applicable).

**Table 2 biomedicines-11-02150-t002:** Neurocognitive measures.

Domain	Measures	Study Period		
		Baseline	Post-Acute	6 Months
Estimated Intelligence Quotient (IQ)	WASI (Vocabulary, Matrix)	x	x	x
Attention/executive functioning; cognitive flexibility and cognitive processing speed	TMT (A & B) and FDT	x	x	x
Verbal and visual episodic memory	RAVLT and BVMT-R	x	x	x
Semantic memory and verbal fluency	FAS	x	x	x
Working memory	Foward and Reverse DGS (WAIS-III)	x	x	x
Cognitive Screening	MoCA	x	x	x
Autobiographical Memory	AMT	x	x	x
Prospective and Retrospective Memory	PRMQ	x	x	x

WASI, The Wechsler Abbreviated Scale of Intelligence [42]; TMT (A and B), Trail Making Test versions A and B [43]; FDT, Five Digit Test [44]; RAVLT, Rey Auditory Verbal Learning Test [45]; BVMT-R, Revised Brief Visuospatial Memory Test [46]; FAS, Verbal Fluency [47]; DGS—WAIS-III, Digit Span—The Wechsler Adult Intelligence Scale, Third Edition-III [48]; MoCA, Montreal Cognitive Assessment [49]; AMT, Autobiographical Memory Task [32]; PRMQ, Prospective and Retrospective Memory Questionnaire [50].

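### The HAMD17 non-inferiority contrast names no covariate although baseline HAMD17 is held for every patient, so precision is given up on the endpoint that sets the sample size

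*Protocol article*

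**What the plan says.** For the HAMD17 comparison, section 2.9 of the protocol article states that "non-inferiority will be assessed by calculating the difference between the means of groups E and C and its 95% confidence interval" at session 12, which is then set against the non-inferiority margin. It names no model, baseline term or covariate. The next paragraph of the same section gives the Autobiographical Memory Task (AMT) co-primary a longitudinal model with age, schooling and treatment-resistant depression as covariates. The same type of model is then extended to all continuous secondary outcomes.

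Baseline HAMD17 exists for everyone. Section 2.3 requires "baseline HAMD17 score ≥17" for entry, and the HAMD17 row of Table 1 is marked at all six time points, including screening and baseline: "HAMD17 x x x x x x".

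Section 2.10 sizes the trial on this endpoint with "α = 0.025 (one-tailed), β = 0.2, and a standard deviation of 9.5" and a margin taken from a meta-analysis of ECT against sham, "with an NI value of 5.7". It arrives at 88 evaluable patients and enrols 100. The AMT comparison is said to need only 26.

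**The concern.** The baseline value of the outcome is usually the first covariate considered for a continuous endpoint in a randomised trial. Here it costs nothing to collect, yet it is absent from the one analysis that drives the sample size, while the other co-primary and the secondary outcomes get fuller models. Success requires both co-primaries, and by the article's own planning HAMD17 is the demanding one, with power of just 80%. What is at stake is the width of the interval compared with a margin that the article itself calls large, and some protection against a chance difference in baseline severity between arms of about 44.

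**Working it through.** **Inputs from section 2.10:** one-sided alpha 0.025, power 0.80, SD 9.5, margin 5.7, 88 evaluable patients (44 per arm).

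**Assumptions, not in the article:** a true difference of 0; a correlation r between baseline and session-12 HAMD17 of 0.2 to 0.5; SD 9.5 read as the SD of the session-12 score.

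**Step 1. Reproduce the plan's figure.**
n per arm = 2 × (1.96 + 0.8416)² × 9.5² / 5.7² = 2 × 7.849 × 2.778 = 43.6, rounded up to 44, so 88 in total. This matches exactly, and 88 / 0.90 = 98, which agrees with an enrolment of 100. A noncentral-t calculation gives 45 per arm, which is immaterial. The stated size is therefore that of a simple two-sample comparison, and it is correct for that purpose.

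**Step 2. Precision without a covariate.**
SE = 9.5 × √(2/44) = 2.025. Half-width = 1.96 × 2.025 = 3.97. Power = Φ(5.7/2.025 − 1.96) = Φ(0.85) = 80.4%.

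**Step 3. Precision with baseline HAMD17 as covariate.**
Residual SD = 9.5 × √(1 − r²), with the SE, half-width and power formulas as in step 2. The single degree of freedom spent on the covariate is ignored.

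| r (assumed) | Residual SD | SE | 95% half-width | Power at 44 per arm | Total N for 80% power |
|---|---|---|---|---|---|
| 0 | 9.50 | 2.03 | 3.97 | 80.4% | 88 |
| 0.2 | 9.31 | 1.98 | 3.89 | 81.9% | 84 |
| 0.3 | 9.06 | 1.93 | 3.79 | 83.9% | 80 |
| 0.4 | 8.71 | 1.86 | 3.64 | 86.7% | 74 |
| 0.5 | 8.23 | 1.75 | 3.44 | 90.1% | 66 |

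**Step 4. How much of a chance baseline imbalance reaches the estimate.**
An imbalance of 1.96 standard errors in baseline HAMD17 shifts the unadjusted session-12 difference by r × 9.5 × √(2/44) × 1.96 = r × 3.97. That is 0.8 points at r = 0.2, 1.2 at 0.3, 1.6 at 0.4 and 2.0 at 0.5, against a margin of 5.7.

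**Step 5. If 9.5 is the SD of change scores.**
Section 2.10 does not say which SD is meant, and the Discussion describes the primary outcome as a reduction in symptoms. With equal SDs at the two times, the ANCOVA residual SD is 9.5 × √((1 + r)/2). At r = 0.3 this is 7.66, giving SE 1.63 and power of about 94%. At r = 0.5 it is 8.23, giving SE 1.75 and power of about 90%. ANCOVA gains precision under this reading too.

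**The case against.** The strongest reply is that nothing here is wrong. Under randomisation a difference of means is unbiased, its confidence interval already allows for chance imbalance, type I error is not inflated, and the sample size was built for exactly this comparison. All of that stands, and it limits the point to one of efficiency.

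A second reply is that a journal article may leave covariates to the analysis plan, and that an ANCOVA estimate is also a difference of means. The article never calls the contrast unadjusted. This stands in part. Because the same section does list covariates for AMT, the plain reading is that HAMD17 has none, but the accurate statement is that none is named.

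A third reply concerns the size of the gain. The article gives neither a correlation nor a baseline SD, and the entry rule sets a floor of 17, which truncates the baseline range and may keep r low. At r = 0.2 power rises by only about 1.5 percentage points. This also stands.

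A reader might go further than the text allows in three ways:

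- **That a baseline imbalance carries over in full to the non-inferiority result.** It does not. Step 4 shows that only a fraction set by r reaches the estimate, and the interval already covers that variation.
- **That randomisation is unstratified and diagnosis must therefore be adjusted for.** Section 2.1 describes random blocks and is silent on stratification. Section 2.3 admits unipolar and bipolar depression with different resistance thresholds ("Conversely, for TRD in bipolar depression, only one prior treatment failure will be required"), but nothing in the article shows that diagnosis predicts HAMD17 here, so no gain from that covariate can be claimed.
- **That the treatment-resistance covariate in the AMT model is constant, since every participant has resistant depression.** This follows only if it is a yes/no term. Section 2.3 grades resistance by failed adequate trials on the ATHF, so a graded covariate is the more sensible reading. It is a separate matter of wording and does not bear on HAMD17.

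**Conclusion.** The point holds as a free improvement, not as an error. The analysis as written is valid and reaches its stated 80% power. It forgoes precision on the endpoint that sets the sample size. For an assumed r of 0.2 to 0.5, the half-width would fall by 0.08 to 0.53 points (3.97 − 3.89 and 3.97 − 3.44), and power at 88 evaluable patients would be 82% to 90%. These figures rest on a true difference of zero, on 9.5 being the endpoint SD and on a correlation that the article does not supply. The direction of the gain does not depend on which SD was meant, but its size does.

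**What to change.** Prespecify, before unblinding, that the session-12 MST minus ECT difference in HAMD17 and its 95% confidence interval come from an ANCOVA with baseline HAMD17 as covariate. The session-12 contrast of the longitudinal model already planned for the other outcomes, with the same covariate, would serve equally well. Compare that interval with the 5.7-point margin in both the modified intention-to-treat and per-protocol samples. Report the unadjusted difference as a sensitivity analysis. State whether the SD of 9.5 refers to the session-12 score or to change.

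The sample size should stay as planned; any gain then becomes a reserve of power. The cost is wording only, since the covariate is already collected.
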